### 10.3 Analysis Populations

The analysis populations in this study include the modified Intention-To-Treat (mITT) and the Per-Protocol Set (PPS).

- **Modified Intention-To-Treat (mITT):** All subjects who are enrolled and receive at least one treatment will be included in this analysis set. mITT is the primary analysis set for efficacy analysis in this study.
- **Per-Protocol Set (PPS):** Includes only participants who fully adhered to the trial protocol (e.g., completed treatment, complied with visits, and had no major violations).

### 10.4 Handling of Missing Data

If the baseline date is missing, it will be imputed with the last available date. For missing dates after baseline due to early withdrawal, right censoring will be applied. The censoring date will be determined by the principal investigator after a case-by-case review of post-treatment laboratory tests.

Other missing baseline indicators and safety data will not be imputed.

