### **2.2 Research Indicators**

#### **2.2.1 Primary Endpoint**

Proportion of subjects with complete response (defined as no vomiting and no rescue medication within 7 days after receiving the study drug).

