# **10 Data Analysis and Statistical Methods**

## **10.1 Sample Size Estimation**

Based on previous studies of 8-12 mg DEX plus NEPA for CINV prevention [8,10], a CRR of 80% was assumed for the control group (8D DEX group). The non-inferiority margin was set at 15%. For the sample size calculation, the CRR in the experimental group (5D DEX group) was also assumed to be 80% under the null hypothesis of non-inferiority. Using a normal approximation method for non-inferiority testing of proportions (Z-test, unpooled, one-sided  $\alpha=0.05$ , power=80%), a total of 176 participants (88 per group) was calculated to be sufficient to demonstrate non-inferiority. To account for a potential 5% attrition rate, the enrollment was increased to 186 participants (93 per group). The sample size calculation was performed using PASS 2021 software.

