### 10.5 General Principles for Efficacy Analysis

In this study, unless otherwise specified, efficacy data will be descriptively summarized according to the following general principles:

- Demographic and clinical characteristics were analyzed using descriptive statistics, with categorical variables expressed as frequencies (percentages) and continuous variables as median (interquartile range).

- The efficacy endpoints (CRR, TCR, and CCR) were analyzed for noninferiority using a stratified Mantel-Haenszel approach to compare dose cohorts, adjusting for age. The combined risk difference and its two-sided 95% confidence interval were calculated. Noninferiority was concluded if the lower confidence limit exceeded the pre-specified margin of -15%. Changes in response within subjects across different treatment phases were assessed using McNemar's test. P values for noninferiority tests were reported as one sided, whereas other P values were two sided.
- Group comparisons employed chi-square/Fisher's exact tests for binary variables, Mann-Whitney U test for continuous variables, and Kruskal-Wallis test for multicategorical data.

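### Right censoring at an investigator-chosen date cannot be applied to a binary 7-day response, so the outcome of patients who withdraw before a recorded failure is left to unblinded judgement

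*Protocol*

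**What the plan says.** Section 2.2.1 of the Protocol defines the primary endpoint as "Proportion of subjects with complete response (defined as no vomiting and no rescue medication within 7 days after receiving the study drug". Section 10.5 analyses CRR, TCR and CCR by a Mantel-Haenszel approach stratified by age: "The combined risk difference and its two-sided 95% confidence interval were calculated". Non-inferiority is concluded if the lower limit lies above -15%. No efficacy endpoint in sections 2.2.1 to 2.2.4 is a time to event.

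Section 10.4 deals with a missing baseline date and then with early withdrawal: "For missing dates after baseline due to early withdrawal, right censoring will be applied". It continues: "The censoring date will be determined by the principal investigator after a case-by-case review of post-treatment laboratory tests". It closes by saying that other missing baseline indicators and safety data are not imputed. It does not say how a patient whose 7-day response is unknown is counted.

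Three other places bear on this:

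- Section 10.2 describes an open-label trial in which all investigators know the allocation.
- Section 10.3 puts every enrolled patient with at least one treatment in the mITT set, the primary efficacy set.
- The synopsis describes an mITT set that may leave out patients with no post-baseline data, and section 5.4 also allows patients to be left out of the final analysis.

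**The concern.** Right censoring belongs to time-to-event analysis, where a patient contributes follow-up until the censoring date. A risk difference between proportions needs a yes or a no for each patient in the denominator. A patient who withdraws on day 2 without vomiting or rescue must be called a failure, called a responder or left out, and a censoring date does not decide among these.

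The date itself rests on the wrong information and the wrong person. Laboratory tests do not measure vomiting or rescue use, and the principal investigator knows the arm. In practice, how such a patient enters the primary analysis could be settled one patient at a time with the allocation in view.

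The non-inferiority decision is at stake. If more patients leave the 5 mg arm because of poor control, excluding them or treating them as event-free hides failures in that arm and favours non-inferiority. Section 1.3.1 concedes that the lower dose may control CINV less well, so uneven dropout is plausible, though the Protocol has no data on it.

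**Working it through.** **Inputs from the Protocol.** Section 10.1: "a CRR of 80% was assumed for the control group (8D DEX group"), "the CRR in the experimental group (5D DEX group) was also assumed to be 80"%, "The non-inferiority margin was set at 15"%, one-sided alpha 0.05, power 80%, 88 per group evaluable, 5% attrition, 93 per group enrolled. Section 10.5: two-sided 95% interval, limit -15%.

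**The plan's own figure.** n per group = (1.645 + 0.842)² × (0.80×0.20 + 0.80×0.20) / 0.15² = 6.183 × 0.32 / 0.0225 = 87.9, so 88. Then 88 / 0.95 = 92.6, so 93 per group and 186 in all. The figures reproduce. Planned attrition is 0.05 × 186 = 9.3, about 9 patients.

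**Worked splits.** Assumptions: 9 dropouts, all without a recorded failure; about 80% response among completers; the split by arm is mine, since the Protocol gives only the total. The interval is unstratified because no age strata are given:

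lower limit = (p₅ − p₈) − 1.96 × √[p₅(1−p₅)/n₅ + p₈(1−p₈)/n₈]

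For 7 vs 2 with dropouts as failures: p₅ = 69/93 = 0.742, p₈ = 73/93 = 0.785, standard error 0.0622, so −0.043 − 1.96 × 0.0622 = −0.165.

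| Dropouts, 5 mg vs 8 mg | Counted as failures | Excluded | Counted as responders |
|---|---|---|---|
| 5 vs 4 | 71/93 vs 71/93: 0.0, lower −12.2% | 71/88 vs 71/89: +0.9, lower −10.8% | 76/93 vs 75/93: +1.1, lower −10.2% |
| 6 vs 3 | 70/93 vs 72/93: −2.2, lower −14.4% | 70/87 vs 72/90: +0.5, lower −11.3% | 76/93 vs 75/93: +1.1, lower −10.2% |
| 7 vs 2 | 69/93 vs 73/93: −4.3, lower −16.5% | 69/86 vs 73/91: 0.0, lower −11.7% | 76/93 vs 75/93: +1.1, lower −10.2% |

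Of these three splits, only 7 vs 2 makes the conclusion depend on the handling.

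**False non-inferiority rate.** 400,000 simulated trials per row, 93 per arm, true rates 80% and 65% (a true difference of −15 points), every dropout assumed to be a true non-responder. The nominal rate is 2.5%, because the decision uses a two-sided 95% interval.

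| Dropout, 5 mg vs 8 mg | As failures | Excluded | As responders |
|---|---|---|---|
| 5% vs 5% | 2.5% | 2.0% | 2.6% |
| 5% vs 0% | 2.5% | 7.9% | 12.3% |
| 8% vs 2% | 2.6% | 9.6% | 17.0% |

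Equal dropout causes no material inflation here; unequal dropout does.

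**The reverse check.** With equal dropout unrelated to response, counting dropouts as failures multiplies both rates by the same factor and shrinks the difference. At 5% dropout, −15 points becomes 0.95 × −15 = −14.25. Simulated, the false non-inferiority rate rises to 3.2% at 5% dropout and 4.1% at 10%, while exclusion stays near 2.5%.

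**The case against.** The strongest reply is that section 10.4 speaks of missing dates. It never says that a patient with an unknown response is excluded or counted as a responder. A reader might infer one or the other, but the text does not support it, and section 10.3 points away from exclusion by keeping all treated patients in the primary set. This stands: the consequence is an undefined outcome, not a stated wrong one. It does not save the sentence, which prescribes a technique that the planned analysis cannot use. A missing-response rule may be left to a statistical analysis plan; an inapplicable rule already written in the Protocol is a different matter.

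A reader might also call this the only rule for missing post-baseline data. That goes too far, since section 10.4 also covers safety data.

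Many early leavers are not missing at all. Treatment is given once, before chemotherapy, and a patient with vomiting or rescue recorded before leaving is a non-responder under section 2.2.1 whatever happens later. Only those who leave before a recorded failure are affected. This stands and narrows the problem.

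The 7 vs 2 example is a selected case: milder splits of the same 9 patients change nothing. A reader might infer that the rule will produce a false non-inferiority claim. The documents do not support that, because they say nothing about dropout by arm or its link to response.

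Last, failure imputation is not neutral. The reverse check confirms this, so a supporting analysis has to be required.

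**Conclusion.** The concern holds in a limited form. Section 10.4 applies right censoring to withdrawals in a trial whose efficacy endpoints are all proportions. It lets an investigator who knows the arm set the date from tests that carry no information on the outcome. The primary outcome of a patient who withdraws before any recorded failure is therefore open to unblinded judgement.

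The size depends on assumptions. At the planned 5% attrition, a 7 vs 2 split moves the lower limit from −11.7% (excluded) to −16.5% (failures), across the −15% margin; 5 vs 4 and 6 vs 3 do not cross it. The error rates of 9.6% and 17.0% require 8% vs 2% dropout with every dropout a true non-responder. With low attrition over a 7-day, single-cycle observation, this should be fixed, but it is not a fatal flaw.

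**What to change.** For CRR, TCR and CCR, delete the right-censoring sentence and the investigator-set date from section 10.4. In their place state:

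- In the mITT analysis (all treated patients, as in section 10.3), a patient without a complete 0-168 h record and with no recorded failure counts as a non-responder. For each phase endpoint the same rule applies to that phase.
- A complete-case analysis, and a worst-case analysis (missing counted as failure in the 5 mg arm and success in the 8 mg arm) or a tipping-point analysis, are required support for a non-inferiority claim.

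Reconcile the synopsis definition of mITT, and section 5.4, with section 10.3.

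The cost is a few sentences and two extra tables, and slightly lower CRR. The main rule also has the drawback shown above under equal, non-informative dropout; the worst-case analysis guards against it. That analysis is strict. In the 5 vs 4 example it compares 71/93 with (71 + 4)/93 = 75/93, a difference of −4.3 points with lower limit −0.043 − 1.96 × 0.0602 = −16.1%, which fails the margin. The sponsor should therefore decide in advance whether the worst case must itself pass, or whether a tipping-point analysis showing how extreme the missing outcomes would have to be is the required support.

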### 10.5 General Principles for Efficacy Analysis

In this study, unless otherwise specified, efficacy data will be descriptively summarized according to the following general principles:

- Demographic and clinical characteristics were analyzed using descriptive statistics, with categorical variables expressed as frequencies (percentages) and continuous variables as median (interquartile range).

- The efficacy endpoints (CRR, TCR, and CCR) were analyzed for noninferiority using a stratified Mantel-Haenszel approach to compare dose cohorts, adjusting for age. The combined risk difference and its two-sided 95% confidence interval were calculated. Noninferiority was concluded if the lower confidence limit exceeded the pre-specified margin of -15%. Changes in response within subjects across different treatment phases were assessed using McNemar's test. P values for noninferiority tests were reported as one sided, whereas other P values were two sided.
- Group comparisons employed chi-square/Fisher's exact tests for binary variables, Mann-Whitney U test for continuous variables, and Kruskal-Wallis test for multicategorical data.

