|------------------------|-----------------------------------------------------------------------------------------------------------------------------------------------------------------------------------------------------------------------------------------------------------------------------------------------------------------------------------------------------------------------------------------------------------------------------------------------------------------------------------------------------------------------------------------------------------------------------------------------------------------------------------------------------------------------------------------------------------------------------|
|                        | 
 
Experimental Group: Intravenous injection of 5 mg dexamethasone 0.5 hours before chemotherapy and oral administration of single dose of NEPA (each containing 0.3 g netupitant and 0.5 mg palonosetron hydrochloride) 1 hour before chemotherapy.
 
 
Stratification Factors: Gender, age, CINV risk factors, ECOG score, tumor type, distant metastasis of the tumor, emetic risk of the chemotherapy regimen, smoking history, alcohol consumption history, etc.
 
Discontinuation Criteria: Discontinue treatment if the patient experiences severe adverse events or specific types of adverse events, such as severe drug intolerance or allergic reactions.
 |
| Study Drugs     | 
 
Dexamethasone Sodium Phosphate Injection
 
Netupitant/Palonosetron Capsules (each containing 0.3 g netupitant and 0.5 mg palonosetron hydrochloride)
 
                                                                                                                                                                                                                                                                                                                                                                                                                                                                                                               |

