### **3.2 Treatment Period**

(1) Control Group: 8 mg of dexamethasone is administered intravenously 0.5 hours before chemotherapy, and 1 tablet of netupitant and palonosetron hydrochloride capsules (each containing 0.3 g of netupitant and 0.5 mg of palonosetron hydrochloride) is taken orally 1 hour before chemotherapy.

(2) Experimental Group: 5 mg of dexamethasone is administered intravenously 0.5 hours before chemotherapy, and 1 tablet of netupitant and palonosetron hydrochloride capsules (each containing 0.3 g of netupitant and 0.5 mg of palonosetron hydrochloride) is taken orally 1 hour before chemotherapy.

Stratification Factors: Gender, age, patient's risk factors for CINV, ECOG score, tumor type, distant metastasis of the tumor, emetogenic risk of the chemotherapy regimen, smoking history, and drinking history, etc.

Drug Discontinuation Criteria During Treatment: Subjects should discontinue the drug if they experience severe adverse events or specific types of adverse events, such as severe drug intolerance or allergic reactions.

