## 4. Selection and Withdrawal of Study Subjects

### 4.1 Inclusion Criteria

Subjects must meet all the following inclusion criteria to be enrolled in this study:

1. Age 18-75 years old.
2. Diagnosed with malignant tumors and undergoing chemotherapy regimens with moderate to high emetogenic risk.
3. ECOG score 0-1.
4. Expected survival of  $\geq 12$  weeks at screening and able to receive the current anti-tumor treatment for at least one cycle.
5. Adequate organ function meeting the following criteria:
  - a: Neutrophil count  $\geq 1.5 \times 10^9/L$ ;
  - b: Platelet count  $\geq 100 \times 10^9/L$ ;
  - c: In patients without known liver metastases, aspartate aminotransferase  $\leq 3 \times$  ULN and/or alanine aminotransferase  $\leq 3 \times$  ULN (for patients with liver metastases, it can be relaxed to  $\leq 5 \times$  ULN);
6. Eligible subjects of childbearing age must agree to use reliable contraceptive measures throughout the study period (including male or female condoms, contraceptive foams, gels, films, creams, suppositories, abstinence, and intrauterine devices, etc.), except for female subjects who have undergone

hysterectomy, bilateral salpingectomy, bilateral tubal ligation, or have been postmenopausal for more than one year, and male subjects who have undergone bilateral vasectomy or ligation.

7. Voluntary participation in this study, signing the informed consent form, and good compliance.

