## **10.2 Randomization and masking**

Computer-generated randomization (SPSS v26.0) assigned 186 patients using a reproducible seed number (2000000). A sequence of random values ranging from 0 to 1 was generated for all 186 participants. Allocation was performed strictly in the order of this pre-generated sequence: the first 93 participants corresponding to the smallest

random values were assigned to the 5D DEX group, and the remaining 93 to the 8D DEX group. This sequential assignment based on a computer-generated random list ensured the randomness of allocation. Investigators enrolled eligible participants and allocated them according to this computer-generated randomization sequence. This open-label study maintained full allocation transparency to all investigators and participants throughout the single-cycle observation.

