| High emetic risk
(>90% frequency of emesis)         | 
 
• AC combination defined as any chemotherapy regimen that contains an anthracycline and cyclophosphamide
 
• Carboplatin AUC <math>\geq 4</math>
 
• Carmustine >250 mg/m^2
 
                                                                                                                                                                                                                              | 
 
• Cisplatin
 
• Cyclophosphamide >1500 mg/m^2
 
• Dacarbazine
 
• Doxorubicin <math>\geq 60</math> mg/m^2
 
• Epirubicin >90 mg/m^2
 
• Fam-trastuzumab deruxtecan-nxki
 
                                                                                                                   | 
 
• Ifosfamide <math>\geq 2</math> g/m^2 per dose
 
• Mechlorethamine
 
• Melphalan <math>\geq 140</math> mg/m^2
 
• Sacituzumab govitecan-hziy
 
• Streptozocin
 
                                                      |
| Moderate emetic risk
(>30%–90% frequency of emesis) | 
 
• Aldesleukin >12–15 million IU/m^2
 
• Amifostine >300 mg/m^2
 
• Bendamustine
 
• Busulfan
 
• Carboplatin AUC <4
 
• Carmustine <math>\leq 250</math> mg/m^2
 
• Clofarabine
 
• Cyclophosphamide <math>\leq 1500</math> mg/m^2
 
• Cytarabine >200 mg/m^2
 
• Dactinomycin
 
• Daunorubicin
 
 | 
 
• Dinutuximab
 
• Doxorubicin <60 mg/m^2
 
• Dual-drug liposomal encapsulation of cytarabine and daunorubicin
 
• Epirubicin <math>\leq 90</math> mg/m^2
 
• Idarubicin
 
• Ifosfamide <2 g/m^2 per dose
 
• Irinotecan
 
• Irinotecan (liposomal)
 
• Lurbinectedin
 
 | 
 
• Melphalan <140 mg/m^2
 
• Methotrexate <math>\geq 250</math> mg/m^2
 
• Mirvetuximab soravtansine-gynx
 
• Naxitamab-gqgk
 
• Oxaliplatin
 
• Romidepsin
 
• Temozolomide
 
• Trabectedin
 
 |

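### The protocol lists nine stratification factors, but allocation uses none and the primary analysis uses only age, so emetic risk (HEC/MEC) enters neither

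*Protocol*

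**What the plan says.** - **Synopsis, Study Design row:** "Stratification Factors: Gender, age, CINV risk factors, ECOG score, tumor type, distant metastasis of the tumor, emetic risk of the chemotherapy regimen, smoking history", followed by alcohol history and an open-ended 'etc.'. That makes nine named factors.
- **Section 3.2:** the same nine, ending "emetogenic risk of the chemotherapy regimen, smoking history, and drinking history, etc".
- **Section 10.2:** "A sequence of random values ranging from 0 to 1 was generated for all 186 participants". By rank, the 93 smallest "random values were assigned to the 5D DEX group, and the remaining 93 to the 8D DEX group". No strata, blocks or minimisation are described.
- **Section 10.5:** CRR, TCR and CCR are compared by a "stratified Mantel-Haenszel approach to compare dose cohorts, adjusting for age". Non-inferiority is concluded if the lower limit of the two-sided 95% confidence interval for the combined risk difference lies above -15%.
- **Section 4.1 and Appendix 2:** patients on moderately or highly emetogenic regimens are both eligible. Appendix 2 separates the classes by emesis frequency: ">90% frequency of emesis" for high risk, and above 30% up to 90% for moderate risk.

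**The concern.** A reader of the synopsis or section 3.2 would expect the listed factors to be used in allocation, in the analysis, or in both. Section 10.2 uses none of them. Section 10.5 uses one and does not say why age was kept and the other eight dropped.

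The omission that matters most is emetic risk. The population deliberately mixes two emetic-risk classes, the endpoint is emesis and rescue use, and the protocol names this factor itself. If complete response differs between HEC and MEC patients, a chance difference in case mix between the arms moves the estimated risk difference, and an analysis stratified by age does not take it out. The precision that stratification would give is also lost.

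There is a further cost in an open-label trial. With nine factors called stratification factors in one place and one factor used in another, more than one adjusted analysis could later be defended from the text.

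**Working it through.** **1. Factors named against factors used**

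| Place | Factors | Emetic risk included? |
|---|---|---|
| Synopsis and 3.2 | 9 named, plus 'etc.' | Yes |
| Allocation, 10.2 | 0 | No |
| Efficacy analysis, 10.5 | 1 (age) | No |

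This mismatch needs no assumption.

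**2. The plan's own sample size**

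Inputs from section 10.1: 80% response in both arms, margin 0.15, one-sided alpha 0.05, power 80%, unpooled Z-test. The calculation reproduces exactly: 88 per arm, 176 in total, and 176/0.95 = 185.3, rounded up to 186. Nothing here disputes that figure.

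The decision rule in 10.5 is a two-sided 95% interval, so it is the basis for the power figures below. At 88 per arm without emetic-risk strata:

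SE = sqrt(2 × 0.80 × 0.20 / 88) = 0.0603; power = Φ(0.15/0.0603 − 1.96) = Φ(0.528) = 70.1%.

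The distance between this and the planned 80% comes from the different alpha in 10.1 and 10.5. That is a separate matter and adds no weight to this point.

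**3. Chance imbalance in the HEC share**

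The document does not give the HEC share; 50% is assumed. With 93 HEC patients among 186 and 93 per arm, the HEC count X in one arm is hypergeometric:

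- Var(X) = 93 × 0.5 × 0.5 × 93/185 = 11.69, SD 3.42.
- The between-arm difference in share is (2X − 93)/93, with SD 2 × 3.42/93 = 7.4 points.
- P(absolute difference of 10 points or more) = 14.2%.

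At 88 per arm with 88 HEC patients, the SD is 7.6 points and the probability 17.5%. HEC shares of 30% or 70% at 93 per arm give an SD of 6.7 points and a probability of 15.0%. Because counts are discrete, one HEC patient more or fewer than exactly half moves the probability to about 19% at 93 per arm and 23% at 88.

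**4. Effect on the estimate**

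Shift = imbalance × HEC/MEC gap in complete response. The gap is not in the document either. For a 10-point imbalance, gaps of 10, 20 and 30 points shift the estimate by 1, 2 and 3 points, against a 15-point margin.

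**5. Effect on power**

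With half HEC and overall response 80%, stratifying by emetic risk reduces the per-patient variance from 0.16 to 0.16 − gap²/4. At 88 per arm, SE = sqrt(2 × variance/88), and power follows as in step 2:

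| Assumed gap | Variance | SE | Power by formula | Gain over 70.1% | Simulated, without → with emetic-risk strata |
|---|---|---|---|---|---|
| 10 points | 0.1575 | 0.0598 | 70.8% | 0.7 | 70.3% → 71.0% |
| 20 points | 0.1500 | 0.0584 | 72.9% | 2.8 | 70.6% → 73.3% |
| 30 points | 0.1375 | 0.0559 | 76.5% | 6.4 | 70.6% → 77.1% |

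Formula and simulation agree on gains of about 1, 3 and 6 points. In both, the comparator has no strata, so age is treated as having no prognostic value.

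**6. Type I error**

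Simulation at 93 per arm with a true difference of −15 points (40,000 runs per setting) gave one-sided error of 2.5% to 2.7% without emetic-risk strata and 2.7% with them, against a nominal 2.5%.

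**The case against.** **No threat to validity.** Unstratified 93:93 randomisation balances emetic risk in expectation, and the confidence interval already allows for chance imbalance. A reader might infer from the missing factor that the comparison is biased or emetic risk is confounded. The documents do not support that, and step 6 shows no material error inflation. This part of the objection stands in full.

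**The list may never have been meant for allocation.** It sits under the treatment description, and section 10.2 claims randomness, not balance. It would therefore be wrong to say that a promised balance is absent. Likewise, nine two-level factors would make 2^9 = 512 cells for 186 patients, but only under full cross-classification, which the protocol never proposes. What stands against the plan is the label: neither place calls these baseline or subgroup variables, and the word used does not fit 10.2.

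**The size rests on assumptions.** Appendix 2 does not establish the gap: its bands of emesis frequency cannot be response rates on this prophylaxis, given the 80% planned in 10.1. Section 1.2 cites complete response above 95% in the acute and delayed phases in HEC patients given 8 or 12 mg dexamethasone with NEPA, which points towards a smaller gap. At 10 points, the gain is under one point of power. This stands, and is why the range is shown. If age is prognostic, the existing adjustment also recovers some precision that these figures do not credit.

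**An SAP could settle it.** Age cut-points and supplementary adjusted analyses can properly be left there, and their absence is no fault. But the protocol itself fixes the allocation method and the age-only adjustment, and both are at odds with its own list.

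**Conclusion.** The inconsistency is certain and depends on no assumption: nine named factors, none in allocation, one in the analysis, and emetic risk in neither.

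The statistical consequence is modest. Chance imbalance in HEC share goes uncorrected, with a 14% chance (93 per arm) or 17% chance (88 per arm) of 10 points or more if half the patients are HEC. The forgone power is about 1, 3 or 6 points for gaps of 10, 20 or 30 points. Both the HEC share and the gap are assumed. There is no systematic bias and no type I error inflation. This should be corrected because the correction is nearly free and removes an ambiguity about the primary analysis; the trial's validity does not hang on it.

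**What to change.** 1. **Synopsis and section 3.2:** remove the stratification label, or present the list as baseline and subgroup variables, closed rather than ending in 'etc.', so that it matches the unstratified allocation in 10.2.
2. **Section 10.5:** stratify the primary Mantel-Haenszel risk difference by emetic risk (HEC/MEC by Appendix 2) together with age in fixed bands. The cut-points can be set in the SAP, before any outcome comparison.

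The cost is one changed analysis line and slightly sparser strata. Two emetic classes by two age bands, for example, make four strata averaging 176/4 = 44 patients. Emetic risk must already be established for eligibility, so no new data are needed.

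The randomisation need not change. Permuted blocks within strata are debatable in a single-centre, open-label trial, because upcoming assignments can become predictable; the analysis change recovers the precision without that risk.

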## 1.2 Current Treatment and Research Status of CINV

The current guidelines recommend a multimodal regimen for preventing nausea and vomiting induced by moderately to highly emetogenic chemotherapy, typically including a 5-HT3 RA, an NK-1 RA, and multi-day dexamethasone, with or without olanzapine.

In a multicenter, placebo-controlled, Phase III study, Ito Y TT et al. conducted a non-inferiority trial comparing single-day versus multi-day standard-dose dexamethasone in patients receiving HEC. The results showed that when combined with an NK1-RA and palonosetron, dexamethasone could be tapered in the subsequent days without additional drug toxicities (46.9% vs. 44.0%, 95% CI, 212.6%-6.8%; P=0.007) [7]. However, this study reported that in the delayed phase, the complete control rate was higher in the 3-day dexamethasone group than in the single-day standard-dose group, suggesting that a 3-day dexamethasone regimen might be more appropriate for patients with risk factors for CINV. Subsequently, Celio L and Cortinovis D et al. validated the non-inferiority of shortening the dexamethasone course in patients receiving high-dose cisplatin, achieving study endpoints across all time intervals in this clinical trial [8]. As early as 2014, R.J. Gralla et al. conducted another Phase III study, demonstrating that NEPA, when combined with DEX, had a slight but consistent numerical advantage (2%-7%) in the total complete response (CR) rate over aprepitant plus palonosetron in consecutive cycles [9].

There are limited studies on reducing the dosage of DEX, and thus the appropriate dosage of antiemetics when NEPA is combined with MEC or HEC remains uncertain. A recent study published in 2023 showed that when patients received a single dose of 8 or 12 mg DEX on Day 1 before each HEC cycle, combined with single-day NEPA treatment, complete response rates of >95% were observed in both the acute and delayed phases, with all patients achieving a 100% CR rate from the third cycle onward [10]. A randomized Phase III study by Celio L et al. showed that neither of the two reduced-dose DEX groups demonstrated a significant impact of vomiting on the daily life of patients receiving high-dose cisplatin, with a DEX dose of 12 mg in DEX1 [11]. Another recently published Phase III study also confirmed the efficacy and safety of 12 mg DEX plus NEPA in elderly patients receiving cisplatin, with similar CR rates across treatment groups [12].

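### The -15% non-inferiority rule in 10.5 is not limited to the primary endpoint, so a margin supported only at 80% overall CRR also serves secondary and exploratory conclusions

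*Protocol*

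**What the plan says.** Section 10.1 sizes the trial on one endpoint. For the 8 mg arm "a CRR of 80% was assumed for the control group (8D DEX group"), the 5 mg arm "was also assumed to be 80% under the null hypothesis of non-inferiority", and "The non-inferiority margin was set at 15" per cent. No other rate or margin appears there.

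Sections 2.2 and 7 rank the efficacy endpoints:

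- 7-day (0-168 h) CRR is primary.
- CRR in the acute, delayed and long-delayed phases is secondary.
- TCR and CCR, each in those three phases and overall, are exploratory.

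Section 10.5 then treats them together: "The efficacy endpoints (CRR, TCR, and CCR) were analyzed for noninferiority", by a Mantel-Haenszel risk difference with a two-sided 95% interval. The rule follows: "Noninferiority was concluded if the lower confidence limit exceeded the pre-specified margin of -15" (per cent), with one-sided P values for the non-inferiority tests. It names no period, gives no second margin and does not make any conclusion depend on the primary result.

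On likely phase rates, section 1.2 reports from one cited study of single-dose 8 or 12 mg dexamethasone with NEPA that "complete response rates of >95% were observed in both the acute and delayed phases".

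**The concern.** An absolute margin means different things at different response rates. Fifteen points set beside 80% response is a moderate loosening. The same 15 points in a period where nearly everyone responds can hide a multiple of the control failures. Because 10.5 fixes one conclusion rule for all three endpoint families, a report that follows it can state non-inferiority for endpoints the protocol itself calls secondary or exploratory, using a margin never argued for them. It can do so even if the 7-day CRR misses.

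This bears on the trial's purpose. Section 1.3.1 recognises that the lower dose may control CINV less well. A pre-specified statement that acute control is non-inferior would be read as reassurance on exactly that risk.

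**Working it through.** **Inputs.** Control and experimental CRR 80%, margin 15 points, "Z-test, unpooled, one-sided" alpha 0.05, power 80%, 5% attrition (10.1). Two-sided 95% interval and -15% limit (10.5). Endpoint list (2.2). Phase control rates are not given. I assume 80% (the overall planning rate), 90%, and 95% (from the study cited in 1.2).

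**1. The plan's own figure.** n per arm = (z₀.₉₅ + z₀.₈₀)² × [0.8×0.2 + 0.8×0.2] / 0.15² = (1.645 + 0.842)² × 0.32 / 0.0225 = 87.9, so 88 per arm and 176 in total. 176 / 0.95 = 185.3, so 186. Both match 10.1, so the 15 points are tied to an 80% rate. (The interval in 10.5 works at one-sided 0.025, not 0.05. That is a separate matter.)

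**2. How many conclusions the rule allows.** Overall period only: CRR, TCR, CCR = 3. All periods in 2.2: CRR 1 + 3, TCR 4, CCR 4 = 12.

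**3. What the margin tolerates.** Ratio of failures = (1 - p + 0.15) / (1 - p), where p is control response.

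| Control response | Failures, control to margin | Ratio |
|---|---|---|
| 80% | 20% to 35% | 1.75 |
| 90% | 10% to 25% | 2.5 |
| 95% | 5% to 20% | 4.0 |

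**4. What data would pass.** Unstratified Wald interval, 88 per arm, 84/88 control responders. With 78/88 on the experimental arm the difference is -6.8 points. SE = √(0.886×0.114/88 + 0.955×0.045/88) = 4.05 points, so the lower limit is -6.8 - 1.96×4.05 = -14.7%. Non-inferiority is concluded with 10 failures against 4. With 77/88 the lower limit is -16.1% and the rule fails.

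**5. How often a true doubling of failures passes.** Sum the product of the two binomial probabilities over all outcomes whose Wald lower limit exceeds -15%.

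| True rates (experimental vs control) | 88 per arm | 93 per arm |
|---|---|---|
| 60% vs 80% (20% to 40% failures) | 0.4% | 0.3% |
| 80% vs 90% (10% to 20% failures) | 16% | 17% |
| 90% vs 95% (5% to 10% failures) | 71% | 74% |

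For 88% vs 95% the figures are 50% and 53%. At the rate used to plan the trial, the rule almost never passes a doubling of failures. At 95% it passes one about seven times in ten.

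**The case against.** **The text names no phases.** Section 10.5 lists three endpoints, and its singular margin points back to 10.1, where only overall CRR is planned. On that reading there are 3 comparisons and the acute-phase problem disappears. This stands as an open reading, which is why the count is 3 to 12. It does not remove the point: two of the three are labelled exploratory, and nothing in 10.5 rules out the phases.

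**The 95% rate is borrowed.** It comes from one cited study, which the reference list titles a retrospective evaluation. The protocol's own figures are 80% (10.1) and about 85% total response in the group's earlier work (1.2). This also stands, and the size must be shown as a range.

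**A 5-point deficit lies inside the margin.** Declaring non-inferiority there is therefore not an error under the stated rule. That is correct. The pass rate shows how loose the unargued margin is, not a false-positive rate. Nor would a true fourfold rise usually pass: at 80% vs 95% it does so in about 3% of trials.

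**Ranking and testing order.** The endpoints are ranked elsewhere in the protocol, and testing order is often left to an analysis plan. Agreed. The point is the blanket rule that 10.5 does state, not a missing multiplicity section.

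**Two stronger readings are not supported.**

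- A reader might compute 1 - 0.975¹² = 26% as the chance of some false conclusion. That needs 12 independent comparisons, all exactly at the margin. The endpoints are nested: total control implies complete control, which implies complete response, and overall response requires response in every phase. Independent falls from 95% to 80% in three phases would put the overall deficit at 0.95³ - 0.80³ = 85.7% - 51.2%, about 35 points, so the overall comparison could not also be at the margin.
- A reader might infer that nausea-control failures could double unnoticed. The protocol gives no TCR or CCR rate. Both are stricter than CRR, so at 80% overall CRR their overall rates cannot exceed 80%, and the margin there tolerates at most 1.75 times the failures.

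**Conclusion.** The point holds, as a cheap improvement. Section 10.5 allows between 3 and 12 non-inferiority conclusions on one margin that is supported only at 80% overall CRR, without requiring the primary to succeed first. If acute control response is near 80%, the margin means there what it means for the primary. If it is near 95%, the margin tolerates up to four times the failures, and a true doubling is declared non-inferior in about 71-74% of trials. Those pass rates assume an unstratified Wald interval and 88-93 per arm. The age-stratified analysis may shift them somewhat.

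A reader should not infer that the primary conclusion is compromised. There is one primary endpoint, and its error rate is not inflated by the others.

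**What to change.** In 10.5, limit the -15% conclusion rule and the one-sided non-inferiority P value to 7-day (0-168 h) CRR in the primary analysis set. State that phase CRR, TCR and CCR are reported as Mantel-Haenszel risk differences with two-sided 95% confidence intervals and without a non-inferiority conclusion.

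If the sponsor wants a formal phase claim, name one phase CRR, test it only after the primary succeeds, and justify a margin for that phase's expected control rate.

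The change is one sentence. It needs no new data, visits or participants, and every estimate is still reported. The cost is that no formal non-inferiority claim can be made for secondary or exploratory endpoints.
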